### Randomisation

Prior to randomisation and treatment, the investigator or design will review baseline data to reconfirm that the participant is safe to receive trial treatment and continues to fulfil the eligibility criteria. Randomisation should be performed before the participant is due to receive their first trial treatment infusion, allowing sufficient time for treatment preparation. Randomisation should only occur for whom the eligibility criteria can be confirmed.

### Treatment day 1 and 2

Participants will be under strict medical supervision in hospital for the treatment visit. The total dose of trial treatment will be given over two consecutive days by intravenous infusion.

Treatment day 1 will be ≤6 ±3 weeks from T1D diagnosis. Changes to health and medications since the baseline visit should be checked including a SARS-CoV-2 test, and blood pressure, heart rate, oxygen saturation, respiratory rate and temperature will be recorded. The participant should also be physically examined for evidence of current infection prior to administration of premedication. It is recommended that concomitant medication with heparin and hydrocortisone, and premedication with corticosteroid, antihistamine and acetaminophen, is given as described in the MELD-ATG Pharmacy Manual, to limit ARs from peripheral ATG/placebo infusion. Blood glucose levels may be affected by premedication and will be managed by the responsible investigator.

The first part-dose of 0.5 mg/kg or 0.1 mg/kg ATG, or placebo of the same volume, will be given as an intravenous infusion over a minimum of 12 hours. AEs throughout the infusion until the end of the visit will be recorded. At the end of the infusion, blood will be collected for FBC, clotting studies (PT and APTT), if PT and/or APTT were abnormal but not beyond exclusion criteria at the screening visit, as well as renal and liver function. The FBC will be reviewed in order to confirm that it is safe to continue with the second treatment infusion.

The second treatment infusion will be given no sooner than 12 hours and no later than 24 hours after the end of the first infusion, over a minimum of 8 hours. As on day 1, vital signs (including blood pressure, heart rate, oxygen saturation, respiratory rate and temperature) will be recorded before administration premedication. Any changes to health and non-trial (excluding insulin) medications during treatment day 1 should also be checked. It is recommended that participants receive premedication as on treatment day 1, as described in the MELD-ATG Pharmacy Manual.

#### Monitoring post-treatment before discharge

During the infusion, vital signs (including blood pressure, heart rate, oxygen saturation, respiratory rate and temperature) will be recorded every 30 min for the first 2 hours, followed by every 60 min or as indicated for clinical signs or symptoms. AEs throughout the infusion until the end of the visit will be recorded as they develop. Guidance on management of the infusion site, CRS, allergic reaction, serum sickness and haematological effects is provided below. At the end of the infusion, blood will be collected for FBC, clotting studies (PT and APTT), if PT and/or APTT were abnormal but not beyond exclusion criteria at the screening visit, as well as renal and liver function.

### Subsequent assessments: follow-up visits 1–6

The following assessments are performed at every follow-up visit: general physical exam, blood pressure, heart rate, temperature, respiratory rate, diabetes care (including insulin regimen and diabetic ketoacidosis), changes in medications and vaccinations, changes in AEs, a SARS-CoV-2 test and urine pregnancy test for WOCBP (follow-up visits 2–6 only). Blood samples will be collected for CD4+/CD8 +T cell count ratio determination and exploratory studies (Omics). Follow-up visit 1 will take place 1-week post end of treatment (±1 day) and the recurring assessments listed above will be carried out.

Follow-up visit 2 will take place 2 weeks post end of treatment (±1 day) while follow-up visit 3 will take place 4 weeks post end of treatment (±1 day). In addition to the aforementioned recurring assessments, safety blood samples will be collected for FBC, clotting studies (PT and APTT), if PT and/or APTT were abnormal but not beyond exclusion criteria at the screening visit, as well as well as renal and liver function for safety monitoring. There will be regular contact between participants and parent/legal guardians and the research team between 2 and 4 weeks post-treatment to monitor AEs, particularly development of serum sickness.

At follow-up visits 4, 5 and 6 (3, 6 and 12 months post-treatment), participants will have a 120 min MMTT during which blood will be collected for measuring glucose and C-peptide. For MMTT measurements please see details in online supplemental appendix below.

Participants will be fitted with a CGM device at follow-up visits 4, 5 and 6 (3, 6 and 12 months post-treatment) and requested to collect CGM measurements for 14 days after each visit. CGM devices (CE marked) will be provided by DexCom Inc. (USA) for use in MELD-ATG and training will be provided to the participant/responsible adult prior to first use. For monthly DBS samples taken at home please see details in the online supplemental appendix below.

Follow-up visit 4 will take place 3 months post end of treatment (±3 weeks). CGM will be collected by the participant for 14 days post visit. Participants will be advised to arrive having fasted for 8 hours. Water is allowed. In addition to the aforementioned recurring assessments, height and weight, changes in family medical history, safety blood samples for FBC, clotting studies (PT and APTT), if PT and/or APTT were abnormal but not beyond exclusion criteria at the screening visit, as well as renal and liver function for safety monitoring will be collected. In addition, research blood samples will be collected for HbA1c (if a result is not available from standard of care testing within ±2 weeks of the visit), along with MMTT as described above, as well as urine (±1 week) and stool samples (±1 week).

Follow-up visit 5 will take place 6 months post end of treatment (±3 weeks). CGM will be collected by the participant for 14 days post visit. Participants will be advised to arrive having fasted for 8 hours. Water is allowed. In addition to the aforementioned recurring assessments, height and weight, and changes in family medical history. In addition, research blood samples will be collected for HbA1c (if a result is not available from standard of care testing within ±2 weeks of the visit), along with MMTT as described above, as well as urine (±1 week) and stool samples (±1 week).

Finally, follow-up visit 6 will take place 12 months post end of treatment (±3 weeks). CGM will be collected by the participant for 14 days post visit. Participants will be advised to arrive having fasted for 8 hours. Water is allowed. In addition to the aforementioned recurring assessments, height and weight, and changes in family medical history. In addition, research blood samples will be collected for HbA1c (if a result is not available from standard of care testing within ±2 weeks of the visit) and T1D-associated autoantibodies (GADA, IAA, IA-2A and ZnT8A) along with MMTT as described above, as well as urine (±1 week) and stool samples (±1 week).

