### Clinical data in T1D

The efficacy of low dose ATG (Thymoglobuline) in T1D has been previously reported in three clinical studies where ATG was used as monotherapy as well as in combination therapy with Granulocyte colony-stimulating factor (G-CSF). In one clinical study, a single low dose ATG (2.5 mg/kg) was given to participants with established T1D (diagnosis 4–24 months; age range 12–45 years) in combination with G-CSF (36 mg) which resulted in C-peptide preservation for up to 18 months, and improved HbA1c^23 24^ and the 5-year follow-up data just published.^29^ Furthermore, in another clinical trial in participants with new-onset T1D (within 100 days from diagnosis; age range: 12–45 years), a single low dose ATG (2.5 mg/kg) alone vs its combination with G-CSF (36 mg in adults and adjusted for children <45 kg who then received 100 mg/kg per dose) resulted in an 18 months lasting beneficially therapeutic outcome, as defined by C-peptide preservation and HbA1c improvement.^26^ Most recently, Haller *et al* reported a 1-year and 2-year clinical trial outcome data confirming a sustained effect of low dose ATG (2.5 mg/kg) treatment on C-peptide preservation and HbA1c improvement.^25^ In contrast, in the trial the Study of Thymoglobulin to ARrest T1D, a higher dose of ATG (6.5 mg/kg) treatment in participants with new-onset T1D failed to achieve β-cell functional preservation.^30 31^ The dose dependent differences in β-cell preservation capacity of ATG encourage further investigation to determine the lowest effective dose of ATG in the treatment of new-onset T1D.

ATG safety data in paediatric population are limited but indicate no fundamentally difference to that seen in adults^22^ as the treatment is applied per body weight. Thymoglobulin adverse events (AEs) are generally manageable or reversible. AEs previously reported with low dose (2.5 mg/kg) ATG treatment in new-onset T1D (age 12–45 years) participants include immune system disorders such as cytokine release syndrome (CRS-with symptoms of fever, headaches, nausea), lymphopaenia and serum sickness. The latter is the consequence of the rabbit IgG nature of ATG. Most reported symptoms may occur seven to fifteen days after onset of treatment. Slow intravenous drug infusion and premedication (eg, hydrocortisone, heparin, corticosteroid, antihistamine, paracetamol) have been shown to manage those symptoms.^22 26^

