1. To determine the effects of ATG treatment on stimulated C-peptide	1. The area under the stimulated C-peptide response curve over the first 2 hours of an MMTT measured throughout the study in different ATG dosage groups	1. Baseline, 3, 6, 12 months
2. To determine the effects of ATG treatment on HbA1c	2. HbA1c measurements measured throughout the study in different ATG dosage groups in mmol/mol	2. Baseline, 3, 6, 12 months
3. To determine the effects of ATG treatment on intermittent CGM measures	3. CGM measures (time in range, time above, time below) measured throughout the study in all different ATG dosage groups and placebo	3. For 14 days at 3, 6, 12 months
4. To determine the effects of ATG treatment on fasting and stimulated DBS C-peptide measurements	4. DBS C-peptide measurements measured throughout the study in all different ATG dosage groups and placebo in pmol/L at 0 min and 60 min	4. Baseline, monthly
5. To determine whether ATG treatment mediates a reduction in CD4-positive T cells but relative preservation of CD8-positive T cells	5. CD4-positive T cells and CD8-positive T cells measured throughout the study in different dosage groups	5. Baseline, 1, 2, 4 weeks and 3, 6, 12 months
6. Descriptive analysis of the safety profile of different doses of ATG in different age groups	6. Safety will be assessed at each visit by physical examination, including assessment of the most commonly reported reactions to ATG, namely serum sickness, CD4 + lymphocyte decrease, cytokine release syndrome, fever, influenza-like symptoms and rash; vital signs (temperature, blood pressure, heart rate); weight, abnormal laboratory parameters (liver, kidney function, full blood count); reporting of adverse events in different dosage groups	6. Baseline, treatment day 1 and 2, 1, 2, 4 weeks and 3, 6, 12 months
7. To determine the effects of ATG treatment on T1D-associated autoantibodies (GADA, IAA, IA-2A and ZnT8A)	7. T1D-associated autoantibodies (GADA, IAA, IA-2A and ZnT8A) at the start and end of the study	7. Screening, 12 months
8. To determine the effects of ATG treatment on insulin requirements	8. Insulin requirements measured throughout the study in all different ATG dosage groups	8. Baseline, 1, 2, 4 weeks and 3, 6, 12 months
Exploratory objectives		

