### Intervention summary

The total dose of ≤2.5 mg/kg ATG will be split into two separate part-doses for intravenous administration over two consecutive days. On treatment day 1, the first infusion of 0.5 mg/kg or 0.1 mg/kg ATG, or placebo of the same volume, will be given over a minimum of 12 hours. On treatment day 2, the second part-dose will be infused over a minimum of 8 hours, commencing between 12 and 24 hours after the first part-dose. A maximum of 60 hours from the start of the first infusion will be allowed to complete all trial drug administration, otherwise the infusion will be discontinued, and no further trial drug will be administered. The trial pharmacist will be responsible for calculating the dose for the participants according to their weight and to the randomisation cohort the participant has been allocated to via the electronic randomisation system, as detailed in the below section ‘Randomisation and blinding’. The weight of the participant at the baseline visit will be used to calculate the dose amount which can be rounded up or down to the nearest ml. The placebo (0.9% sodium chloride solution) will be sourced from local hospital stock. There will be an identical volume of infusion solution between ATG and placebo dosages, and identical labelling will be used for the ATG infusion bag and placebo.

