Other allergic reactions to trial treatment infusion may be managed based on the severity of the allergic reaction. A mild (≤grade 1–2) allergic reaction will allow trial medication to be restarted at the discretion of the investigator. With either a severe (grade 3) reaction or a life-threatening (grade 4) allergic reaction, trial medication should be permanently discontinued. In case of anaphylaxis (begins at CTCAE grade 3 or higher), the trial treatment infusion should be terminated immediately, and appropriate emergency treatment should be initiated. Equipment for emergency therapy for anaphylactic shock must be readily available.

Serum sickness from host immunisation against rabbit protein may occur 7–15 days after the first dose of ATG. It is a reaction that is similar to an allergy. Signs and symptoms can take as long as 14 days after exposure to appear, and may include signs and symptoms commonly associated with hypersensitivity or infections including rashes, itching, arthralgia (especially finger and toe joints), fever (as high as 40°C and usually appears before rash), lymphadenopathy (particularly near the site of injection, head and neck), malaise, hypotension, splenomegaly, glomerulonephritis, protein or blood in the urine or shock. The participants than may require glucocorticoid treatment for supportive care. The dose will depend on the severity of signs and symptoms and guidance is provided in the MELD-ATG Trial Manual. The least amount of steroid required to provide symptomatic relief of serum sickness, due to the effect of glucocorticoid on blood glucose.

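### Regular contact for serum sickness is set at 2–4 weeks post-treatment and so misses the protocol's own usual onset period (days 7–15); starting it at follow-up visit 1 is a cheap improvement

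*Protocol article*

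**What the plan says.** **Onset.** The section Toxicity management states: "Serum sickness from host immunisation against rabbit protein may occur 7–15 days after the first dose of ATG". Clinical data in T1D agrees, listing serum sickness among the reactions and adding: "Most reported symptoms may occur seven to fifteen days after onset of treatment".

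**Contact.** The section Subsequent assessments: follow-up visits 1–6 places regular contact between the research team and participants or parents "between 2 and 4 weeks post-treatment to monitor AEs, particularly development of serum sickness". The same section times follow-up visits 1 and 2 at one and two weeks after the end of treatment, each ±1 day.

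**Other surveillance.** Table 1, secondary objective 6, provides that "Safety will be assessed at each visit by physical examination, including assessment of the most commonly reported reactions to ATG, namely serum sickness" and other listed reactions. Evaluation of AEs has adverse events recorded from consent onward, and Source data lists a participant diary.

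**Treatment duration.** Intervention summary: "A maximum of 60 hours from the start of the first infusion will be allowed to complete all trial drug administration".

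**Care.** Toxicity management, on serum sickness: "The participants than may require glucocorticoid treatment for supportive care".

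**The concern.** The stated purpose of the contact is to pick up the development of serum sickness, yet its window opens as the protocol's usual onset period closes. Most of that period falls between follow-up visits 1 and 2, where the text provides no regular contact.

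Two things are at stake.

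- **Participant care.** The reaction may need glucocorticoids, and the trial enrols from age 5. The section Trial participants, study design and oversight says that ATG has not yet been used in this indication and at these doses at ages 5–11. A case recognised late is a case treated late.
- **Safety data.** Known drug reactions and interaction with other therapies describes the reaction as brief. An episode that starts and fades between two visits leaves its onset date and peak grade to recall.

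Serum sickness is also common. That section gives 72.4% in the earlier low-dose trial. If the rate carried over (an assumption, since that trial enrolled ages 12–45), about 0.724 × 32 = 23 of the 32 participants needed at 2.5 mg/kg would be affected.

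**Working it through.** The protocol gives no coverage figure to reproduce. The check puts all timings on one clock, with day 0 as the start of the first infusion.

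**Inputs**
- Usual onset: days 7–15, an 8-day span (Toxicity management; Clinical data in T1D).
- First infusion at least 12 h; gap to the second 12–24 h; second infusion at least 8 h (Treatment day 1 and 2). All dosing done within 60 h (Intervention summary).
- Follow-up visits 1, 2 and 3 at 1, 2 and 4 weeks after the end of treatment, each ±1 day. Contact from 2 to 4 weeks post-treatment (Subsequent assessments: follow-up visits 1–6).

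**End of treatment**
- Earliest: 12 + 12 + 8 = 32 h = day 1.33.
- Latest: 60 h = day 2.5.

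**Contact period and its overlap with onset**
- Start: 14 + 1.33 = day 15.33 to 14 + 2.5 = day 16.5.
- End: 28 + 1.33 = day 29.33 to 28 + 2.5 = day 30.5.
- Overlap with days 7–15: 0 of 8 days. The near edge is missed by 15.33 − 15 = 0.33 to 16.5 − 15 = 1.5 days.
- If post-treatment is counted from the first dose: 15 − 14 = 1 of 8 days.
- If the 7–15 days are instead counted from the end of treatment, the reading kindest to the plan: again 15 − 14 = 1 of 8 days.

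**Onset days between the two visits (nominal timing)**

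| | Treatment lasts 32 h | Treatment lasts 60 h |
|---|---|---|
| Visit 1 | 7 + 1.33 = day 8.33 | 7 + 2.5 = day 9.5 |
| Visit 2 | day 15.33 | day 16.5 |
| Onset days between visits | 15 − 8.33 = 6.67 | 15 − 9.5 = 5.5 |

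These are calendar days, not shares of cases.

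**Delay in recognition if the family does not report**
- Maximum: 7 days nominal; 7 + 1 + 1 = 9 days at the window limits.
- Mean, if onset is uniform over the onset days between the visits: visit 2 − (visit 1 + 15)/2.
  - 32 h: 15.33 − 11.67 = 3.67 days.
  - 60 h: 16.5 − 12.25 = 4.25 days.
- Mean at the window limits:
  - Lowest (32 h, visit 1 late, visit 2 early): 14.33 − (9.33 + 14.33)/2 = 2.5 days.
  - Highest (60 h, visit 1 early, visit 2 late): 17.5 − (8.5 + 15)/2 = 5.75 days.

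**With contact from visit 1**
- Overlap: 15 − 9.5 = 5.5 to 15 − 8.33 = 6.67 of 8 days.
- Still uncovered: 8.33 − 7 = 1.33 to 9.5 − 7 = 2.5 days before visit 1.
- With calls every 2–3 days (assumed), the mean delay is half the interval: 1–1.5 days.

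**The case against.** The strongest reply is that surveillance in the onset period rests on visits, not calls. Visit 1 falls inside the period and visit 2 just after it. Both include a physical examination, temperature and adverse-event review, and visit 2 adds blood count, renal and liver function. Visits are weekly up to week 2 and then 14 days apart (12–16 with windows), so placing contact in the longer gap is a coherent choice that catches late onset and the course of earlier episodes. **This stands**: monitoring is not absent, and the existing contact should stay.

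The onset limits are also soft. The text says only that symptoms may occur then, and adds that signs can take up to 14 days after exposure. At 2.5 mg/kg most of the dose comes with the second infusion, so the late edge could reach the start of the contact period. **This stands for the late edge only.** It does not cover the days between visits 1 and 2.

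The article is condensed, and the Trial Manual may schedule earlier calls. **This stands as a limit**: the manual is not visible and is not judged here. If it already starts earlier, the protocol sentence should be brought into line with it.

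Finally, a family would probably call about high fever or rash, and in the earlier trial no case was grade 4 and none led to readmission. **This stands in part**: the delays above are upper bounds. The reassurance is weaker for ages 5–11, whom that trial did not enrol.

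**Conclusion.** The point holds, as an optional improvement. On the protocol's own timings the stated contact covers 0 of the 8 usual onset days, and 1 of 8 at most when the reference point is moved from the end of treatment to the first dose. The 5.5–6.7 onset days between visits 1 and 2 have no stated contact.

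The consequence is a possible delay of at most 7 days in recognising a case (9 at the window limits), and less exact onset dates and grades in a descriptive outcome. The mean delay of 3.7–4.3 days (2.5–5.8 with windows) rests on uniform onset, because no onset distribution is given, and on no self-report. Cases would still be recorded at the visits. The number of cases, the primary comparison, power and error control are untouched.

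**What to change.** Amend the sentence in Subsequent assessments: follow-up visits 1–6 so that regular contact runs from follow-up visit 1 (about one week post-treatment) through week 4. Record the date of serum sickness onset at each contact. This keeps the existing cover between visits 2 and 3 and adds the week in which most of the onset period falls. The 1.3–2.5 onset days before visit 1 stay outside it.

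The cost is a one-sentence amendment, a matching update to the Trial Manual, and a few extra calls per participant in the second week by the existing research team.

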### End of trial participation

The end of trial participation is defined as completion of the final follow-up visit. Once complete, the CGM device will be returned to the participating site (may be offered to participants but only if support costs are available locally). Participants enrolled into this trial already receive the appropriate standard of care for T1D, and this care continues after the trial. Following completion of MELD-ATG participation, participants will be offered to join the INNODIA longitudinal study (ClinicalTrials.gov identifier: NCT03936634; www.innodia.eu). Participation in this further study is optional and would involve a separate PIS and ICF/assent form. Participation would allow for data to be collected on the MELD-ATG participants for an additional 12 months delivering 24 months outcome data. Consent would be sought to link MELD-ATG trial data with INNODIA longitudinal study data. Written informed consent will have been sought on joining the trial to confirm that participants, or their appropriate legal representative, give permission to be contacted to inform them of trial results, potential future follow-up, and/or future interventional and/or observational T1D studies organised by the INNODIA consortium.

